**Fig. 2 Fig2:**
[figure not shown]
Summary of phase-II RCT process. GA, general anaesthesia

#### Outcome measures

Fig. 3 outlines the various measures completed in the phase-II RCT. The primary outcome measures are:

**Fig. 3 Fig3:**
[figure not shown]
Outline of measure completion. GA, general anaesthesia

Parent and child satisfaction with the intervention, as indicated using the visual analogue scale.Improvement in the child’s dietary knowledge measured by the change in pictorial dietary quiz score taken at baseline, postintervention, and after 3 months.Change in child’s diet at home, measured by children’s dietary questionnaire taken at baseline and after 3 months.Return of the child’s toothbrushing diary showing their level of engagement in toothbrushing, and return of snack diary showing reported healthy snack selection.

The secondary outcome measures are:Parent and child verbal feedback on intervention in the form of qualitative data.Completion of ‘secret words’ sheet by children in intervention group, indicating use of game DVD at home.Attendance rates for review appointment after three months.

#### Statistical analysis

Descriptive statistics for all explanatory variables at baseline will be provided, overall and by study group. Analysis of variance and chi-square tests will be used to highlight any significant imbalance between groups.

Student’s *t* test will be used to compare the two groups’ parent and child visual analogue scale scores, indicating satisfaction with intervention. It will also be used to compare children’s dietary questionnaire, toothbrushing scores, and healthy snack selection scores. Since the children’s pictorial dietary quiz is the only measure taken at three points (baseline, directly after intervention, and three months later), its scores will be analysed using linear multivariate regression.

Verbal feedback provided by parents and children on intervention will be written down verbatim and will be analysed using simple content analysis.

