#### Participants

The target population will be children referred for extraction of decayed teeth under general anaesthesia. Families will be invited to take part in the study at their child’s attendance at the medical pre-assessment clinic prior to their general anaesthesia appointment.

The inclusion criteria are as follows: the child is four to ten years old, does not have any learning difficulties or medical conditions complicating oral health status and is scheduled for treatment of dental caries under general anaesthesia. A parent or guardian should provide consent and both parent and child should have English proficiency.

The exclusion criteria are as follows: the child is referred for treatment of other dental conditions under general anaesthesia, has learning difficulties or a medical condition affecting oral health, is accompanied by an adult that cannot give consent, or, has been participating in another study. Families where either the parent or guardian or the child do not have sufficient English proficiency to consent or understand the advice delivered will also be excluded.

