#### Randomization and blinding

A computer-generated simple randomization grid will allocate the participants to the two groups. The randomization process will be overseen by the unblinded researcher (MTH). The allocation of participants will be performed by the two trained dental nurses responsible for applying the interventions to the participants. The researcher (AA) will remain blinded all through data collection and input. The statistician will also be blinded during the analysis. Only after data collection is complete will one researcher (MTH) break the randomization code to input the group allocation within the pre-existing data set and enable between-group analyses. The statistician and lead researcher (AA) will remain blinded.

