#### Procedure for recruitment and application of intervention

Each week, the blind researcher (AA) will obtain a list of all children attending the medical pre-assessment clinic for general anaesthesia for dental purposes. Those who are younger than four or older than ten will be excluded.

Next, AA will go through the clinical notes of the remaining children to determine their eligibility to participate. At this stage, children who are having treatment for dental conditions other than caries, or with medical conditions affecting dental health or learning difficulties, and those children participating in other studies can be identified and excluded. All children accompanied by parents or guardians that require an interpreter to provide consent for the general anaesthesia procedure will also be excluded. However, the total number of those children will be recorded. The research will also record the different languages of the non-English speakers. South London is a culturally and ethnically diverse area, and keeping records of the languages spoken by those children and their families will help assess the local area’s future need for versions of the video game in different languages.

On the day of the clinic, AA will approach all potential participants, invite them to take part, and explain the study to them. At this stage, children accompanied by adults who cannot provide consent for them (aunt or uncle, older sibling, *etc*.) and those who do not display enough English proficiency to take part will also be excluded. AA will aim to approach every potential participant matching the inclusion criteria; however, some potential participants will be missed, as they will arrive and leave their appointment while a participant is taking part in the study.

Parents who indicate their agreement to take part will be asked to provide written consent and their child will be asked for assent. AA will then administer three following baseline measures. A pictorial dietary quiz will be completed by the child. This is the same quiz used in the phase-I pilot. (ii) A children’s dietary questionnaire will be completed by the parent. This is a validated measure used to report the dietary habits of children aged 4–16 years [31]. It includes four sections (covering intake of fruit and vegetables, dairy, sweet drinks, and non-core foods). Finally, details of the child’s most recent snack at school will be provided by the child.

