After the baseline measures are completed, AA will introduce the participants to the dental nurse and leave, to ensure that he remains blinded to group allocation. The nurse will then allocate the participants to either the video-game group or the control group according to the randomization grid and will apply the intervention accordingly.

The nurse will administer postintervention measures to both groups including: (i) pictorial dietary quiz, completed by the child; (ii) child’s and parent’s satisfaction with intervention on a visual analogue scale; (iii) a booklet that contains a toothbrushing diary and a snack diary, to be returned on the day of the general anaesthesia procedure. The booklet given to children from the study group will also contain a page in which they can write five ‘secret words’ that have been inserted in the DVD version of the game. This will allow us to determine whether participants used the game DVD at home. Children from the control group will have a simple colouring page instead. Finally, (iv) the nurse will ask the parent and child if they have any feedback on the intervention; this feedback will be written down verbatim (qualitative data).

AA will go to the day surgery unit on the day of the child’s general anaesthesia procedure to collect the booklet. He will also call the participating parents three months after their child’s general anaesthesia procedure and offer them a review appointment at the paediatric dentistry department. Upon attending, the parents of both groups will be asked to complete the children’s dietary questionnaire again, to measure any changes in dietary practices at home. The child will be asked to retake the pictorial dietary quiz to assess long-term retention of dietary knowledge. Attendance rates from both groups will be noted.

Fig. 2 is a summary of the recruitment process and the measures collected.

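### The dietary questionnaire is compared by a t test with no covariate, although its baseline score is collected; a baseline-adjusted model would be more precise

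*Protocol article*

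**What the plan says.** All references are to the protocol article.

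- **Planned test.** Under Statistical analysis, Student's t test is named first for the satisfaction scales. The text then adds: "It will also be used to compare children’s dietary questionnaire, toothbrushing scores, and healthy snack selection scores". No covariate is named.
- **Outcome.** Under Outcome measures, one of the listed primary outcomes is "Change in child’s diet at home, measured by children’s dietary questionnaire taken at baseline and after 3 months".
- **Data collected.** The section on the procedure for recruitment and application of intervention lists the questionnaire among the baseline measures ("A children’s dietary questionnaire will be completed by the parent"), taken before the nurse allocates the family. At the 3-month review, "the parents of both groups will be asked to complete the children’s dietary questionnaire again". The questionnaire has four sections.
- **Where regression is used.** Only the pictorial dietary quiz gets a model: "its scores will be analysed using linear multivariate regression". The reason given is that it alone is measured at three time points.
- **Allocation and imbalance.** "A computer-generated simple randomization grid will allocate the participants to the two groups"; no stratification is described. On imbalance, the plan says: "Analysis of variance and chi-square tests will be used to highlight any significant imbalance between groups". It states no adjustment.

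**The concern.** A pre-allocation measurement of the same quantity by the same instrument is usually the best covariate available, and this trial collects it by design. A baseline plus one follow-up is the standard setting for ANCOVA, so having two time points rather than three is no reason to fall back on a t test.

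The Statistical analysis section also leaves open what is tested. If it is the 3-month score, the baseline is unused. If it is change, which the outcome definition suggests, the baseline is used by subtraction. That fixes its coefficient at 1 instead of letting the data set it.

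At stake is precision on a listed primary outcome for which no sample size was calculated from its own data: the article's calculation rests on the satisfaction scale, with a supporting check on the quiz. Allocation is simple, so chance baseline differences are to be expected, and either t test passes part of such a difference into the estimate.

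**Working it through.** **1. The plan's own figure.** The Sample size section gives SD 25 mm, difference 15 mm (standardised 0.6), 80% power, 5% level and 45 per group. Taken as two-sided, the normal approximation gives 44 per group. The exact noncentral t gives 44.6, rounded up to 45, with power 80.4% at 45. The figure reproduces, but it is for the satisfaction scale. No such figure is stated for the questionnaire.

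**2. Inputs for the comparison.**
- Number analysed: 108 recruited less 20% dropout (Sample size section) is 108 × 0.8 = 86.4, about 43 per arm.
- Correlation r between baseline and 3-month score: not in the article. Assumed 0.3, 0.5 and 0.7.
- Difference: not in the article for this outcome. Assumed 0.5 SD of the 3-month score.
- Equal SDs at both times and a two-sided 5% level: assumed.

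**3. Variance of the estimated difference, relative to a t test on the 3-month score.**
- 3-month score: 1
- Change: 2(1 − r)
- ANCOVA on baseline: 1 − r²
- Hence ANCOVA relative to change: (1 − r²) / [2(1 − r)] = (1 + r)/2

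| r | 3-month score | Change | ANCOVA | ANCOVA saving against 3-month score | ANCOVA saving against change |
|---|---|---|---|---|---|
| 0.3 | 1 | 1.40 | 0.91 | 9% | 35% |
| 0.5 | 1 | 1.00 | 0.75 | 25% | 25% |
| 0.7 | 1 | 0.60 | 0.51 | 49% | 15% |

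Below r = 0.5, change is less precise than ignoring the baseline altogether. ANCOVA beats change for every r below 1, and beats the 3-month score for every r other than 0.

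**4. Power.** The noncentrality is 0.5 / √(2v/43), where v is the relative variance above. There are 84 degrees of freedom for the t tests, less one per covariate for ANCOVA. At r = 0.5, ANCOVA has 0.5 / √(2 × 0.75/43) = 2.68, against 2.32 for either t test.

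| r | 3-month score | Change | ANCOVA |
|---|---|---|---|
| 0.3 | 63.0% | 49.1% | 67.1% |
| 0.5 | 63.0% | 63.0% | 75.4% |
| 0.7 | 63.0% | 84.1% | 89.4% |

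One covariate or two gives the same ANCOVA figures to one decimal.

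**5. Sensitivity to the assumed difference.** Borrowing the satisfaction scale's 0.6 SD and 45 per arm, power for 3-month score / change / ANCOVA is 80/66/84% at r = 0.3, 80/80/90% at r = 0.5 and 80/95/98% at r = 0.7. The ordering is the same.

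**6. Chance imbalance.** Suppose the arms differ by δ at baseline. With equal SDs, the 3-month comparison is shifted by rδ and the change comparison by −(1 − r)δ; ANCOVA removes both under a linear relation. At 43 per arm the standard error of a baseline difference is √(2/43) = 0.22 SD, so δ = 0.2 SD is ordinary (p about 0.36). At r = 0.7 the shifts are 0.7 × 0.2 = 0.14 SD and −0.3 × 0.2 = −0.06 SD.

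**7. Cost of adjusting.** In a simulation at 45 per arm, with baseline and age both in the model and age unrelated to outcome, the ANCOVA variance relative to the 3-month t test was 0.94, 0.76 and 0.51 at r = 0.3, 0.5 and 0.7. At r = 0 it was 1.03, so two useless covariates cost about 3%.

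**The case against.** The strongest reply is that nothing here is invalid. Under randomization a t test on either quantity is unbiased and holds its error rate. That stands. A reader might infer that the planned analysis is biased, or that a baseline imbalance passes in full into the result. Neither follows: the imbalance enters only in part, as step 6 shows, and the loss is one of precision.

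Second, calling the plan unadjusted fits only one reading. Because the outcome is defined as change, the t test is probably on change, so the comparison with the 3-month score may not be the relevant one. Against change, if r is high, the gain is modest: 84% to 89% in step 4, or 95% to 98% in step 5. This also stands, and it is why both readings are shown.

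Third, r and the 0.5 SD difference are assumptions. That is so. The direction of the gain does not depend on them, but its size does.

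Three further inferences are not supported:
- **That this outcome suffers the most dropout.** The quiz is retaken at the same 3-month review, the Discussion also expects imperfect diary return, and it offers telephone follow-up. No outcome-specific dropout is given.
- **That age must be in the model.** Children range from four to ten, but the article links age only to the difficulty of the quiz. All the gain computed above comes from the baseline score.
- **That the baseline significance tests harm this comparison.** They tell little under randomization, but dropping them would change no result for the questionnaire.

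Nor does the point extend to the diaries named in the same sentence, which have no baseline diary.

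**Conclusion.** The point holds as one of efficiency and clarity. The plan fixes a t test with no covariate for a listed primary outcome, does not say which quantity is tested, and passes over a baseline score that it collects. For r between 0.3 and 0.7, ANCOVA saves 9% to 49% of the variance against the 3-month score and 15% to 35% against change. At r = 0.5 the saving is worth a third more children (1/0.75 = 1.33) on either reading. These sizes rest on the assumed r and equal SDs, and the power figures also on the assumed 0.5 SD and 43 per arm. The change is worth making, but the planned analysis is not invalid without it.

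**What to change.** In the Statistical analysis section, take the dietary questionnaire out of the t-test sentence. Replace it with a linear model of the 3-month score on arm and the baseline score of the same section, fitted for each of the four sections, reporting the adjusted difference between arms with its 95% confidence interval. Age may be added as a second covariate if the team expects it to predict diet score; if so, state this in advance. The model also settles whether the analysis is of the 3-month score or of change, because with baseline in the model both give the same arm difference.

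The cost is a change of wording and one degree of freedom, or two with age. No new data, visits or participants are needed.

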#### Sample size

The primary outcome measure in this study is user satisfaction with the intervention, assessed using a visual analogue scale. This is constructed as a continuous 100 mm line, with a score at the 0 mm mark indicating complete dissatisfaction with the intervention and a score at the 100 mm indicating complete satisfaction. As far as we know, this is the first study measuring patient’s satisfaction with the use of video games for oral health education. Assuming that our population will have a standard deviation of 25 mm, which is similar to patient satisfaction measured in studies in other fields [29], and aiming to detect a difference of at least 15 mm between the groups to indicate its clinical significance, a sample of 45 participants in each group will be needed to provide 80 % power, at the 5 % significance level, to detect effects of size 0.6 and above. This number of participants is also sufficient based on our calculations using the results of the pictorial dietary quiz used in the phase-I RCT. Anticipating a 20 % dropout rate [30], we intend to recruit approximately 108 participants.

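### The primary healthy-snack diary score is compared by an unadjusted t test although related baseline data exist; a short prespecified adjusted model is a cheap gain of uncertain, possibly modest size

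*Protocol article*

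**What the plan says.** The protocol article's section on the procedure for recruitment and application of intervention lists three baseline measures: the pictorial quiz, the children's dietary questionnaire completed by the parent, and a snack report, of which it says "Finally, details of the child’s most recent snack at school will be provided by the child". The questionnaire has four sections, two of which cover sweet drinks and non-core foods. All three measures are finished before the nurse allocates the family.

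The snack diary comes later. After the intervention the nurse hands out "a booklet that contains a toothbrushing diary and a snack diary, to be returned on the day of the general anaesthesia procedure". The diary therefore has no baseline version. Outcome measures lists it as primary, in the words "return of snack diary showing reported healthy snack selection".

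Statistical analysis assigns Student's t test to the satisfaction scores and then extends it: "It will also be used to compare children’s dietary questionnaire, toothbrushing scores, and healthy snack selection scores". No covariate is named. The quiz is the only outcome given a regression. On baseline data, the section says "Descriptive statistics for all explanatory variables at baseline will be provided, overall and by study group", followed by tests for imbalance between the groups. It states no action that depends on those tests.

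Randomization and blinding describes simple randomization, with no stratification mentioned.

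**The concern.** The school snack is a pre-allocation report of the behaviour that the diary measures, and the questionnaire's non-core-food section bears on the same behaviour. A t test on the diary score uses neither. If they predict the diary score, a model that includes them gives a narrower interval from the same participants.

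Chance imbalance is the second part. Simple randomization with arms of this size leaves room for the groups to differ in snacking at the start, and nothing in the stated comparison corrects for it. A significance test at baseline may flag such a difference, but it does not remove its effect on the estimate. At stake is the precision of one primary outcome, not its validity.

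**Working it through.** **Reproducing the plan's own figure.** Sample size gives these inputs for the satisfaction scale: "Assuming that our population will have a standard deviation of 25 mm" and "aiming to detect a difference of at least 15 mm between the groups to indicate its clinical significance". The effect size is 15/25 = 0.6. Two-sided testing is assumed, since the article does not state it. The normal formula gives n = 2 × (1.960 + 0.842)² × (25/15)² = 43.6, so 44 per arm. The t-based calculation gives 44.6, so 45. The stated 45 reproduces, and t-test power at 45 per arm is 80.4%.

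This figure belongs to the satisfaction scale. The article gives no effect size, SD or power for the snack diary, so 0.6 SD is used below only as an illustration.

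**Formula for adjustment.** With p covariates whose joint correlation with the diary score is R, the variance of the group difference is multiplied by (1 − R²) × [1 + p/(N − p − 3)]. The second factor is the expected cost of chance covariate imbalance. For N = 90 and p = 2 it is 1 + 2/85 = 1.0235. Power comes from a noncentral t with 88 − p degrees of freedom and noncentrality 0.6 × √(45/2) = 2.846, divided by the square root of the variance multiplier.

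| Joint correlation R (assumed) | Variance multiplier, two covariates | Power |
|---|---|---|
| unadjusted | 1 | 80.4% |
| 0.1 | 0.990 × 1.0235 = 1.013 | 79.8% |
| 0.2 | 0.960 × 1.0235 = 0.983 | 81.0% |
| 0.3 | 0.910 × 1.0235 = 0.931 | 83.0% |
| 0.4 | 0.840 × 1.0235 = 0.860 | 85.9% |
| 0.5 | 0.750 × 1.0235 = 0.768 | 89.5% |

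Break-even is where 1 − R² = 1/1.0235, that is R of about 0.15. With four covariates the cost factor is 1 + 4/83 = 1.048. Power is then 80.1% at R = 0.2 and 82.1% at R = 0.3, so a long covariate list uses up most of a small gain.

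**What correlation is plausible?** The article gives none. Suppose the school snack is scored healthy or not, and the diary score averages k similar snacks. With within-child correlation ICC, the correlation of one snack with the diary score is ICC/√[ICC + (1 − ICC)/k].
- ICC 0.05, k = 7: 0.05/√(0.05 + 0.95/7) = 0.12.
- ICC 0.20, k = 14: 0.20/√(0.20 + 0.80/14) = 0.39.

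Both ICC and k are assumed. Over this range the snack item alone would explain about 1% to 16% of the variance. How much the non-core-food score adds is not known.

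**Chance imbalance.** With 45 per arm, the standard error of a standardized baseline difference is √(2/45) = 0.21. A difference above 0.2 SD in either direction occurs in about 34% of trials, and above 0.3 SD in about 15%. Only the part that correlates with the outcome carries over: an imbalance of 0.3 SD at a correlation of 0.3 shifts the estimate by 0.3 × 0.3 = 0.09 SD.

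**Dietary questionnaire.** The same sentence assigns it a t test, although the same instrument is completed at baseline and at three months. Relative to comparing three-month scores, and ignoring degrees of freedom, the variance is 2(1 − ρ) for change scores and 1 − ρ² for adjustment, where ρ is the baseline to three-month correlation. At an assumed ρ of 0.5 these are 1, 1 and 0.75. The adjusted variance is never above either of the others.

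**The case against.** The strongest reply is that nothing here is wrong. An unadjusted t test is valid under randomization, and its standard error already allows for chance imbalance. Covariate lists are often left to a statistical analysis plan, which is not shown. The covariate is also weak: one recalled snack, reported by a child aged four to ten, with no scoring defined. The Discussion itself warns that diaries may record the expected answer, that some questionnaire items may correlate poorly, and that the questionnaire has not been validated in the UK.

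Most of this stands, and it limits the point to efficiency. It does not remove it, because the article does not leave the method open: it names a test, and that test takes no covariate.

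Three stronger readings are tempting, and the article does not support them.
- A reader might infer that the school snack is never used. The baseline descriptions by group and the imbalance tests would ordinarily include it. What can be said is that it has no part in the stated between-group comparison.
- A reader might take 80.4% as the power for the snack diary. It is the power for the satisfaction scale.
- A reader might take 20% off 45 and work with 36 per arm. The target of about 108 already allows for dropout: 108 × 0.8 = 86.4, or about 43 per arm, where unadjusted power at 0.6 SD is 78.5%. Diary return could be lower, as the Discussion anticipates, but the article gives no figure for it.

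**Conclusion.** The point holds as an efficiency recommendation. The planned comparison of a primary outcome omits pre-allocation information on the same behaviour, and under simple randomization it makes no correction for chance baseline differences.

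For an illustrative 0.6 SD effect, 45 per arm and two covariates, the gain is under 1 percentage point of power at a joint correlation of 0.2, about 3 points at 0.3 and about 9 at 0.5. At about 0.1 there is no net gain. These figures rest on assumed correlations and on an effect size borrowed from another outcome. The improvement is cheap, its size is uncertain and may be modest, and leaving the t test in place would not invalidate the result. The case for adjusting the dietary questionnaire is stronger, because its baseline is taken on the same instrument.

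**What to change.** In Statistical analysis, replace the t test for healthy snack selection with a linear model of the diary score on group. Use two baseline covariates: the school snack scored healthy or unhealthy, and the non-core-food score from the dietary questionnaire. Report the adjusted group difference with its 95% interval. In the same edit, compare the three-month dietary questionnaire by a linear model on group and its own baseline score. Fix the covariates and the scoring of the school snack before the allocation code is broken, and keep the list short.

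The cost is a sentence or two of analysis wording, a scoring rule for one item already collected, and one or two degrees of freedom. No new data, visits or participants are needed, and the plan already uses regression for the quiz.

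### The primary diet outcome is compared by an unadjusted t test on an unspecified score, although a baseline questionnaire is collected that a regression (ANCOVA) would use more precisely

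*Protocol article*

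**What the plan says.** All references are to the protocol article.

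- **Outcome measures** lists among the primary outcomes: "Change in child’s diet at home, measured by children’s dietary questionnaire taken at baseline and after 3 months".
- **Procedure for recruitment and application of intervention** has the baseline form filled in before the nurse allocates the family: "A children’s dietary questionnaire will be completed by the parent". At the 3-month review parents are asked to "complete the children’s dietary questionnaire again, to measure any changes in dietary practices at home".
- **Statistical analysis** gives Student's t test for the satisfaction scales and adds: "It will also be used to compare children’s dietary questionnaire, toothbrushing scores, and healthy snack selection scores". It does not identify the questionnaire score to be compared and names no covariate.
- The same section treats the pictorial quiz differently: "its scores will be analysed using linear multivariate regression". The reason given is that only the quiz is measured at three time points.
- On baseline comparability it says that analysis of variance and "chi-square tests will be used to highlight any significant imbalance between groups". No consequence for the outcome analysis is stated.
- **Randomization and blinding**: "A computer-generated simple randomization grid will allocate the participants to the two groups". No stratification is mentioned.

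**The concern.** Each child has a dietary score before allocation and another at 3 months. The analysis section nevertheless groups this outcome with the diary scores, which are collected only after the intervention, and keeps regression for the quiz because of its third time point. Two time points are enough to adjust for baseline, so that reason does not justify leaving the questionnaire out.

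The article leaves two readings of the t test open.

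- **3-month score.** The baseline is discarded.
- **Change score.** The baseline is used, but with its coefficient fixed at 1. With equal SDs at the two times and r below 1, that over-corrects.

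At stake are the precision of a primary outcome for which the article states no sample size, and the reading of the result if simple randomization happens to leave the arms different at baseline.

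**Working it through.** **Inputs**

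- From Sample size: SD 25 mm ("Assuming that our population will have a standard deviation of 25 mm"), difference 15 mm, 45 per group, 80% power, 5% significance (two-sided assumed), 20% dropout, about 108 recruited. All of these belong to the satisfaction scale.
- Assumed: 43 analysed per arm (108 × 0.8 = 86.4, about 43 each), a true difference of 0.5 SD on the dietary score, equal SDs at the two times, and r from 0.3 to 0.8. The article gives neither an effect size nor r for this outcome.

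**Step 1. Reproduce the plan's own figure.** The standardised difference is 15/25 = 0.6. An exact two-sample t-test calculation at two-sided 5% and 80% power gives 44.6, so 45 per group. Power at 45 is 80.4%. The stated 45 is correct for satisfaction.

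**Step 2. Variance of the estimated difference, relative to a t test on the 3-month score**

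- 3-month score: 1
- Change score: 2(1 − r)
- ANCOVA: 1 − r²

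Since 1 − r² = (1 − r)(1 + r), the ratio of ANCOVA to change score is (1 + r)/2, which is below 1 whenever r < 1. The ratio of ANCOVA to the 3-month score is 1 − r², below 1 whenever r is not 0. ANCOVA is therefore never worse, apart from the negligible cost of estimating one coefficient.

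**Step 3. Power with 43 per arm and 0.5 SD.** The effective standardised difference is 0.5 divided by the square root of the relative variance. At r = 0.5, for example, ANCOVA gives 0.5/√0.75 = 0.577 and the change score gives 0.5/√1 = 0.5.

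| r | Relative variance: change | Relative variance: ANCOVA | Power: 3-month score | Power: change score | Power: ANCOVA | ANCOVA minus change |
|---|---|---|---|---|---|---|
| 0.3 | 1.40 | 0.91 | 63% | 49% | 67% | 18 points |
| 0.5 | 1.00 | 0.75 | 63% | 63% | 75% | 12 points |
| 0.6 | 0.80 | 0.64 | 63% | 73% | 82% | 9 points |
| 0.7 | 0.60 | 0.51 | 63% | 84% | 89% | 5 points |
| 0.8 | 0.40 | 0.36 | 63% | 95% | 97% | 2 points |

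**Step 4. Sensitivity to the assumed effect.** Borrowing 0.6 SD and 45 per arm from the satisfaction calculation, t-test power for 3-month score / change score / ANCOVA is 80/66/84% at r = 0.3, 80/80/90% at r = 0.5, and 80/95/98% at r = 0.7. ANCOVA has the highest power throughout. The gain over the change score is about 18, 10 and 2 points.

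**Step 5. Chance baseline difference.** With 45 per arm, the standard error of the baseline difference is √(2/45) = 0.211 SD. A difference beyond 0.2 SD in either direction then has probability 2 × [1 − Φ(0.2/0.211)] = 34%. Given such a difference, the 3-month test carries r times it into the estimate and the change test carries (r − 1) times it. At r = 0.5 and a 0.2 SD imbalance, that is 0.5 × 0.2 = +0.10 SD and −0.5 × 0.2 = −0.10 SD.

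**The case against.** The strongest reply is that the outcome is defined as change and the repeat questionnaire is described as measuring change. A t test on change scores is then at least as natural a reading as one on 3-month scores, and it does use each child's baseline. This stands. A reader might infer that the planned test ignores baseline altogether, or might size the loss against a 3-month-score test (a detectable difference of 0.61 SD at 80% power with 43 per arm). The article does not support either as a description of its plan, because it does not say which score is tested. The comparison with change scores is the fairer one, and there the gain is small when r is 0.7 or more.

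Second, there is no validity failure. Under randomization both t tests are unbiased on average and keep their type I error; the shifts in Step 5 arise only given a chance imbalance. The article also makes no power claim for diet, so no stated target is missed. This stands too, and it limits the point to precision and conditional bias.

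Third, an article condenses a fuller plan, and covariates are often settled there. This stands only in part. The article names a test for this outcome and gives its reason for confining regression to the quiz, so the choice is stated and not merely left out.

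A reader might also suppose that diet suffers more attrition than the other outcomes. The article does not show this: the quiz is retaken at the same review, the Discussion offers telephone follow-up, and it also expects imperfect return of the diaries.

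**Conclusion.** The concern holds as a recommendation on efficiency and clarity. The analysis section fixes an unadjusted t test for a primary outcome with a baseline measure and leaves open which score is tested. Under either reading, baseline-adjusted regression is more precise for any r between 0 and 1.

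For 43 per arm and 0.5 SD, the gain over a change-score test falls from 18 power points at r = 0.3 to 2 at r = 0.8. Over a 3-month-score test it rises from 4 points (67 − 63) to 34 (97 − 63) across the same range. These sizes rest on the assumed effect, r and equal SDs; the ordering of ANCOVA against the two t tests does not depend on the assumed effect or on which r in this range applies.

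The sentence quoted from the analysis section also covers toothbrushing and snack selection. A reader might extend the criticism to them, but their diaries are issued only after the intervention and the t test leaves no baseline diary score unused.

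**What to change.** In Statistical analysis, take the dietary questionnaire out of the t-test list and add a sentence along these lines: the arms will be compared by linear regression of the 3-month questionnaire score on arm, with the same child's baseline score on the same section as covariate, and the adjusted difference will be reported with its 95% CI.

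This settles which score is analysed and handles chance baseline differences without depending on a significance test of imbalance. The t test can stay for the diary scores as far as this point is concerned.

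The cost is one sentence. It needs no new data, visits or participants. It should be fixed before the allocation code is linked to the outcome data.
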